### Recruitment Process

The recruitment of new participants begins with an initial contact, conducted either in person or by telephone, during which a concise overview of the study’s purpose and procedures is provided. If the prospective participant expresses interest and meets the inclusion criteria, they are invited to proceed with the next steps.

For participants in the PD group, an appointment is arranged at the APM, while control group participants attend a meeting at the Escuela Técnica Superior de Ingenieros Industriales at Universidad Politécnica de Madrid. During these sessions, the study’s objectives, procedures, and expectations are thoroughly explained to ensure participants have a comprehensive understanding of their role and responsibilities.

To formalize their participation, individuals are asked to review and sign an informed consent form in compliance with ethical guidelines and regulatory standards.

### Study Design

This study comprises 1 week of free-living monitoring of 20 participants with PD and 20 healthy control participants. The proposed number of participants in this study is comparable to those found in the literature for defining biomarkers in PD (mean 15, SD 6.8 patients with PD) [28,31,36-39] or for monitoring PD motor symptoms (mean 15.4, SD 4.5 patients with PD) [29,40-45]. Small samples are common in exploratory research with wearable sensors, particularly in populations considered vulnerable and hard to recruit such as individuals with PD. Such studies are important for early validation of methods and identifying key trends to inform future research. While the sample size limits detailed subgroup analyses, it is adequate for assessing general patterns and methodological feasibility. All participants will undergo the same experimental protocol, which includes the following:

A baseline assessment to establish initial measuresA 1-week period of unsupervised free-living activity monitoring to capture naturalistic dataA final evaluation to reassess clinically and compare with baseline results

The study schema is illustrated in Figure 1, providing an overview of the structured protocol and its key phases.

**Figure 1 figure1:**
[figure not shown]
Overview of the experimental protocol of the study.

Participants will engage in a series of standardized exercises and a structured free-living activity conducted at home. The findings from this study will establish a foundation for future research focused exclusively on assessing free-living activities without requiring patients to perform any predetermined tasks.

Upon recruitment, each participant begins the experimental protocol with a meeting at APM (for the PD group) or at the Escuela Técnica Superior de Ingenieros Industriales at Universidad Politécnica de Madrid (for the control group). During this visit, a baseline assessment of the participant’s motor symptoms is conducted using the Monipar set of exercises [46]. This set comprises 8 tasks specifically designed to evaluate various motor symptoms of PD.

Seven of these exercises are adapted from the MDS-UPDRS III scale: resting tremor amplitude (item 3.17), postural tremor of the hands (item 3.15), finger tapping (item 3.4), hand movements (item 3.5), pronation-supination movements of the hands (item 3.6), arising from a chair (item 3.9), and gait (item 3.10). The eighth exercise, proposed by the research team, complements the evaluation by addressing additional motor symptoms. These tasks are routinely used by neurologists in clinical settings, and participants are generally familiar with their performance, ensuring ease of implementation.

For the PD group, a specialized PD physiotherapist performs all the assessments using the MDS-UPDRS III scale to ensure consistency and reliability across participants.

In addition, to facilitate the transition from controlled clinical assessments to unsupervised free-living conditions, participants are required to perform a specific free-living activity. This activity involves beating eggs for 1 minute, a common daily task familiar to most individuals. The repetitive nature of this activity makes it particularly useful for evaluating bradykinesia [47,48] under free-living conditions. The selection of this activity was informed by consultations with nurse practitioners, patients, and therapists, all of whom stated its potential relevance and significance for assessing bradykinesia.

Following the baseline evaluation, participants proceed with the study in free-living, unsupervised conditions, maintaining their normal daily routines. They are required to wear the smartwatch throughout the day for 1 week, removing it only at night for charging. Vanmechelen et al [49] revealed that some participants feel discomfort using wearable devices, particularly at night, due to concerns about privacy and intrusion into daily life.

The smartwatch records accelerometer and gyroscope data during a designated 4-hour period each day. This recording window, determined by the participants at the study’s outset, accommodates their individual schedules and availability. Participants are expected to perform a series of tasks within this defined period, which will remain consistent throughout the 7 days of the study.

In the 4-hour recording period, each participant is asked to perform the Monipar exercises daily under free-living conditions and without supervision. Participants are encouraged to complete the full set of exercises each day, ideally at the same hour of the day.

Completing this set of exercises takes approximately 7 to 8 minutes daily, which does not significantly disrupt patients’ daily lives. Incorporating them as a routine task facilitates easier recall and adherence. In addition, participants will be required to perform the specific free-living activity of beating eggs for 1 minute each day. So, the participants will need to set aside 10 minutes each day to perform these 2 tasks.

In prior clinic-based studies [46], participants reported that they did not perceive the daily performance of these exercises as tedious or repetitive. However, modifications were implemented in the duration of each exercise to mitigate fatigue and to provide users with the flexibility to choose when to complete them. This adjustment is intended to enhance user compliance without compromising data quality.

In addition, participants will complete a daily paper questionnaire to help contextualize the 4-hour recorded sensor data. This questionnaire captures the timing of key activities such as breakfast, lunch, and dinner; rest periods (useful for assessing resting tremors); and medication intake. Participants are also encouraged to include any relevant comments for each day, such as forgetting to wear the smartwatch or if the device was completely discharged.

As participants are required to wear the smartwatch throughout the day, their physical activities, such as walking, running, or cycling, are automatically recorded and labeled by the device using its built-in apps [50]. Physical activities are characterized by step count, distance covered, and calories burned during each session. This automatic labeling allows any physical activity that occurs during the designated 4-hour signal recording period to correlate with the acquired accelerometer and gyroscope data, enhancing the contextual understanding of the recorded measurements.

After 1 week of free-living monitoring, participants return to APM for a final evaluation, conducted in the same manner as the baseline assessment. This includes performing the Monipar exercises under the guidance of the PD physiotherapist (for the PD group); completing the specific free-living activity; and filling out a questionnaire to assess the comfort and usability of the smartwatch, report any issues encountered, and provide additional observations or feedback.

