### Technical Support

At the beginning of their participation in the study, each participant receives a detailed set of instructions designed to facilitate understanding and adherence during the week of free-living monitoring. These instructions primarily consist of image-based guidelines to ensure clarity and ease of comprehension. These visual instructions are provided to each participant in printed form for convenient reference throughout the study. In addition, participants are given the phone number of a research team member, which is prominently displayed on their smartphone wallpaper and included in the instruction materials, allowing them to reach out with any questions or concerns during the study.

In addition, as participants in the PD group are members of the APM, they will receive personalized follow-up regarding their participation in the study. For individuals with whom in-person contact will not be possible, phone calls will be made—upon request—to remind them of specific aspects of the study. Furthermore, the final evaluation questionnaire will include a question regarding the participants’ willingness to receive further follow-up through alerts or calls. Once data collection is complete, a detailed analysis of each participant’s actual follow-up will be conducted to assess adherence to the study protocol.

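### The supervised baseline comparison of PD and control participants is completely aliased with site, and the protocol conflicts with itself on where controls have their final visit

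*Protocol article*

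**What the plan says.** All references are to the Methods of the protocol article unless stated.

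- **Recruitment Process.** For the PD group "an appointment is arranged at the APM, while control group participants attend a meeting at the Escuela Técnica Superior de Ingenieros Industriales".
- **Study Design, baseline.** Each participant starts "with a meeting at APM (for the PD group) or at the Escuela Técnica Superior de Ingenieros Industriales", the latter for controls. A PD physiotherapist scores the PD group on the MDS-UPDRS III.
- **Study Design, final visit.** "participants return to APM for a final evaluation, conducted in the same manner as the baseline assessment". Guidance by the PD physiotherapist is mentioned for the PD group; nobody is named for controls.
- **Data Analysis.** The supervised egg-beating recordings are located at the association, and the school is not mentioned. Biomarkers for identifying PD are to come from comparing patients with healthy participants.
- **Inclusion and Exclusion Criteria.** Age is the only adjustment covariate named.
- **Technical Support.** "as participants in the PD group are members of the APM, they will receive personalized follow-up regarding their participation".
- **Discussion, Limitations.** Differences in site or supervisor between the groups are not mentioned.

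**The concern.** One stated aim is to distinguish PD from healthy controls in supervised as well as free-living settings. If all patients are recorded in one building and all controls in another, a feature that responds to the room, chair or walkway will separate the groups whether or not it reflects disease. A classifier can exploit several such features at once. Because the dataset is to be made public, later users would inherit the problem without being told of it.

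The second issue is internal consistency. Controls cannot return to APM if their baseline was at the school. A reader cannot tell whether the final-visit comparison shares one site or repeats the baseline problem.

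**Working it through.** **Plan's own figure.** The study has "1 week of free-living monitoring of 20 participants with PD and 20 healthy control participants". The number is justified by precedent (for example "mean 15, SD 6.8 patients with PD" in earlier biomarker studies), with no alpha, power or effect size. It cannot be re-derived, and this point does not dispute it. It supplies only the group sizes used below.

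**Step 1: is site separable from group?** Code group = 1 for PD and site = 1 for APM.

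*Baseline, columns [1, group, site].* PD rows are (1, 1, 1) and control rows are (1, 0, 0). The group and site columns are the same, so the rank is 2 of 3 and the two are fully aliased. Adding age does not change this.

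*Final visit and both visits pooled.* The two readings are:

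| Reading for controls' final visit | Final visit alone | Both visits, [1, group, visit, site] |
|---|---|---|
| At the school | Rank 2 of 3, aliased | Rank 3 of 4, aliased |
| At APM (literal wording) | One site only, contrast free of site | Rank 4 of 4, estimable |

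Under the second reading, write a for the intercept and g, v, s for the group, visit and site effects. The cell means are:

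- PD baseline: a + g + s
- PD final: a + g + v + s
- Control baseline: a
- Control final: a + v + s

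The PD change is v and the control change is v + s, so s is identified only as the difference between the two changes, assuming the same visit effect in both groups. The group effect is then (PD final) − (control final) = g. The baseline contrast, g + s, contributes nothing of its own. Adding a group-by-visit term gives rank 4 of 5, and site is aliased again.

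**Step 2: how large could the bias be?** The documents give no site effect, so every shift δ (in SD units) below is an assumption. Assume no disease effect, normal features with equal variance, and 20 against 20.

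- Apparent AUC = Φ(δ/√2).
- False-positive rate = two-sided 5% t test with 38 df and noncentrality δ/√(2/20).

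| Assumed δ | Noncentrality | False-positive rate | Apparent AUC |
|---|---|---|---|
| 0.2 | 0.63 | 9.5% | 0.56 |
| 0.3 | 0.95 | 15% | 0.58 |
| 0.5 | 1.58 | 34% | 0.64 |
| 0.8 | 2.53 | 69% | 0.71 |
| 1.0 | – | not computed | 0.76 |

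These are single-feature values. A model that combines several shifted features could show a larger separation.

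**Step 3: which comparisons are exposed?**

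- Prediction of MDS-UPDRS scores uses PD patients only, so it is not affected.
- Home recordings do not share the visit site. Supervised signals are the reference for judging them, so a site difference could reach the home data indirectly through that quality check.
- Of the seven named tasks adapted from the MDS-UPDRS, five are tremor or hand tasks. Chair rise and gait are the two that plausibly depend on chair or walkway.

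**The case against.** A reader might infer that every supervised PD-versus-control contrast is confounded by site, that the groups are supervised by different staff, and that this contradicts the statement that "All participants will undergo the same experimental protocol". The documents do not support going that far.

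- **Every supervised contrast.** Read literally, the final visit is at APM for both groups, and that contrast is then free of site.
- **Different staff.** The physiotherapist is tied to the PD group, but the controls' supervisor is never named. A condensed article may leave that to the full protocol.
- **The same protocol.** The article defines this by its three components: baseline, one week of monitoring, final evaluation. Both groups have all three. Likewise, conducting the final visit in the same manner as baseline describes procedure, not location. The real conflict is only the named site.
- **Unequal follow-up.** Technical Support describes personalized follow-up for the PD group, but the Limitations section promises follow-up and automated reminders without restricting them to patients. In any case, contacts during the week cannot affect the baseline session.

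The article also contains real safeguards: the same watch and phone, instructions displayed and played by an app, the same standardized instructions for all, and review of supervised signals by at least four experts. These weaken the argument that results depend on who prompts the participant. They do not equalize the room, chair or walkway, and they do not break the aliasing. It is also fair to say that this is an exploratory study with no stated site effect, so bias is possible rather than shown.

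**Conclusion.** Two things are certain from the text. The supervised baseline contrast between PD and controls is completely aliased with site, and adjustment for age or any other covariate cannot repair it. And the statements on where controls are seen conflict: Recruitment Process and the baseline description name the school, while the final-visit description and Data Analysis name only APM.

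Two things are not certain. The final-visit contrast may or may not be aliased, depending on how the conflict is resolved. The size of any bias is unknown: the range of apparent AUC from 0.56 to 0.76 rests wholly on assumed shifts of 0.2 to 1.0 SD, and common devices and app guidance make the smaller values more plausible for hand and tremor tasks than for chair rise and gait.

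The point deserves correction because it touches a stated aim and goes unmentioned among the limitations. It does not invalidate the home-based comparison or the prediction of clinical scores.

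**What to change.** 1. Reconcile Recruitment Process, Study Design (baseline and final visit) and Data Analysis, stating the controls' site and supervisor at each visit.
2. Hold the controls' final visit at APM, as the final-visit text already says, with the same chair, walkway and script as the PD group. If that is not possible, duplicate chair, walkway and script at the engineering school.
3. Record site and supervisor for every supervised session and keep both in the public dataset.
4. Name the home recordings, plus the final visit if it is held at a common site, as the main PD-versus-control dataset.
5. Report the supervised baseline contrast as confounded by site, and add this to Limitations.
6. Apply the same reminder contacts to both groups.

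**Cost.** Items 1, 4 and 5 are wording. Item 3 is two extra fields per session, and item 6 is a few calls. Item 2 means travel for controls who have not finished. Recruitment began in December 2024, so sessions already held cannot be moved, and shifting all control baselines to APM is not realistic. The sponsor would also have to accept a weaker claim for the supervised baseline contrast.

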### Devices Used in the Study

This study uses 2 different types of devices: a smartwatch (Samsung Galaxy Watch5) and a smartphone (Samsung Galaxy A14). The smartwatch serves as the primary measuring tool, responsible for recording all generated data throughout the study. In contrast, the smartphone is used to display instructions and label the proposed activities.

Figure 2 illustrates the devices used in this study. The home screen of the smartphone displays 2 distinct icons representing the apps participants will use to complete the activities. A contact telephone number is displayed on the wallpaper (blurred for privacy purposes). In addition, the smartwatch screen is intentionally designed to display only essential information, such as the time, date, and battery status, to ensure user-friendliness and minimize distractions for participants.

The smartwatch incorporates an LSM6DS0 module, integrating a 3-axis digital gyroscope and a 3-axis digital accelerometer, which facilitate the recording of both acceleration and angular velocity. The smartwatch configuration was set to prevent the collection of unnecessary data, such as location, audio, or video, to ensure data relevance and privacy.

Sensor’s data are captured using an Android Wear OS custom app developed by the research team, configured to acquire data at a sampling rate of 50 Hz from each sensor. This frequency was chosen because it is well suited for analyzing PD motor symptoms, which typically occur within the 0 to 20 Hz range [51].

**Figure 2 figure2:**
[figure not shown]
Devices used in this study: smartphone (left) and smartwatch (right).

In addition, this custom app facilitates the scheduling of accelerometer and gyroscope signal recordings. In this study, a period of 4 hours per day is chosen for the free-living monitoring week. Continuous recording throughout the day is avoided for 2 primary reasons: to preserve participants’ privacy—because certain activities could be inferred from these sensor data—and to minimize battery consumption. With these considerations, data from the accelerometer and gyroscope are recorded for a duration of 4 hours, during which the participants must perform the proposed activities.

In addition, the smartwatch is responsible for collecting data related to the physical activity performed by each participant all day, obtained from the smartwatch’s dedicated apps.

In contrast, the smartphone functions as a user interface, facilitating participants’ execution of both the Monipar activity and the specific free-living activity. This was achieved through 2 dedicated apps designed to display and playback the instructions necessary for performing these tasks effectively.

While the apps were identical in functionality, each was designated for a specific task—one for the Monipar activity and the other for the specific free-living activity. This differentiation served 2 purposes: providing participants with the flexibility to perform each activity at their convenience and accommodating the additional preparation required for the specific free-living activity.

The smartphone synchronizes with the smartwatch; tags each activity performed; and, upon completion of the study with each participant, integrates the data recorded by the smartwatch with these labels. This process ensures accurate data labeling, aligning the sensor measurements with the corresponding activities for subsequent analysis.

The smartphone is set up to prevent the collection of unwanted data, such as location, audio, or video. In addition, participants are restricted from making calls or accessing apps unrelated to the study. To address potential participant inquiries, the phone number of a researcher is set as the device’s wallpaper.

Figure 3 illustrates the interface of the Monipar app, while Figure 4 depicts the layout of the app for the specific free-living activity.

**Figure 3 figure3:**
[figure not shown]
Interface of the app related to the Monipar activity: start screen (left) and activity screen (right).

**Figure 4 figure4:**
[figure not shown]
Interface of the app related to the specific free-living activity: start screen (left) and activity screen (right).

### Data Collection

The proposed system is designed for dual functionality, allowing use in both supervised clinical settings and unsupervised daily-life scenarios. Although all devices involved operate independently, they are temporally synchronized via Bluetooth, ensuring simultaneous data collection and seamless integration of information from multiple sources.

The smartwatch serves as the primary device for recording data, while the smartphone facilitates the capture of time stamps for activity labeling. Data extraction and processing will occur after the study using a desktop computer. Figure 5 illustrates the architecture of the data acquisition system during and after the study.

The smartwatch worn by the participant acquires data from the accelerometer and gyroscope sensors for a duration of 4 hours each day. The data are recorded at a frequency of 50 Hz and stored in a text file in the device memory. Once the specified recording period is completed, the text file is saved in a compressed format (zip), and the original text file is deleted. This compression is done to prevent the risk of memory saturation on the device, as text files take up approximately 4 times the space of compressed files. This ensures that all daily data files are saved and stored on the device without any issues. These compressed files remain on the smartwatch until the device is retrieved at the final study visit.

Physical activity data will be collected using the device’s built-in apps, temporarily stored on the watch, and periodically transmitted via Bluetooth to the smartphone. The smartphone then retains this information until the study concludes.

